#### Usual care

The control group will receive usual care and a leaflet with current physical activity guidelines for cancer survivors [31]. Both intervention groups will have access to the same leaflet via IPAS. The leaflet explains the physical activity guidelines and provides information on how the intensity of moderate to vigorous PA can be monitored by Borg rating of perceived exertion, a “talk-test” (when it becomes more difficult to talk in whole sentences) and heartrate self-monitoring. Although they are not actively referred, participants are not prohibited from participating in a rehabilitation or exercise programs with a physiotherapist in primary care, if they so wish. At 6 months, questions about participation in such programs will be included in the questionnaire.

### Sample size calculation

With a total sample of 195 patients (65 per group), the study will have 80% power to detect an effect size of 0.5 for the primary outcome (change in weekly time spent in MVPA) with a *p* value of 0.05. An effect size of 0.5 typically represents a group difference or change over time that is perceived as being clinically relevant [33].

In total, 246 subjects will be recruited for this study, to allow for an attrition rate of approximately 20% (i.e., subjects who discontinue participation in the study entirely, including failure to complete all follow-up measures; those who discontinue participation in one of the groups but complete the follow-up assessments will be included in the analysis). We did not chose for a forced 50–50% inclusion of breast and prostate cancer survivors. Eligible patients will be included, regardless of the tumor type. Thus, at least 195 subjects will be available for the primary intention-to-treat analysis.

**Table 4 Tab4:** Outcome measures and measurement time points

Outcome	Measured by	Baseline	6 months	12 months	Continuously
PRIMARY					
Physical Activity	Objectively (Accelerometers and GPS-trackers)	x	x	x	
SECONDARY					
Physical Activity	Self-reported (IPAQ)	x	x	x	
Stage of behaviour change	Stage of change	x	x	x	
Fatigue	MFI	x	x	x	
Mood	POMS				
Quality of life	SF-36 and EQ5D	x	x	x	
OTHER OUTCOMES					
Cost outcomes	iMCQ iPCQ		x	x	
Social-demographic and clinical data	Social-demographic questions and patient medical file	x			
Moderators and Mediators of PA	Social-demographic questions and patient medical file	x			
Non-participation data	Reasons of non-participation question + Baseline questionnaire.	x			
Compliance	Questionnaire + Portal log data		x		x
Patient evaluation of the program	Questionnaire		x		
Contamination question for control group	Question on alternative PA program participation		x	x	

### Outcomes measures

#### Primary outcome

The main study parameter is objectively measured PA, using the Actigraph GT3X+ activity monitor (Actigraph, Pensacola, Florida, USA) and a BT-Q1000XT GPS-device (QStarz International Co). The Actigraph is a small tri-axial accelerometer that can measure accelerations from 0.05 to 2.00 G [34]. An instruction leaflet will be provided to explain how both devices should be worn on the right hip. The accelerometers and GPS devices will be initialized to collect data at 5 s intervals during 7 consecutive days. After each period of data collection (at baseline, 6 and 12 months) the devices will be sent back by patients to the research institute via mail. Output (activity counts and GPS data) will be downloaded to a PC after the monitoring period. Weekly time spent in MVPA will be calculated by standard cut-points [35, 36]. GPS-data will be used to better classify PA behaviour, e.g. if the speed of GPS data- points is < 12 km/h, the modality will be set to ‘walking & jogging’, and if the speed of the GPS data-points is ≥12 and < 25 km/h, modality will be set to ‘cycling’. Change in weekly time spent in MVPA between baseline and 6 and 12 months will be used as the main outcome parameter. An overview of primary and secondary outcome measures is provided in Table 4.

#### Secondary outcomes

Secondary outcomes are measured by questionnaires at baseline, 6 and 12 months follow-up. The cost questionnaires will be filled in after 6 and 12 months.

##### Self-reported PA level

The International PA Questionnaire (IPAQ) will be used to assess self-reported PA during the past seven days in five activity domains (i.e. job related, transportation, household activities, recreational activities and sedentary activities).

Total MET (Metabolic Equivalent of Task) score in MET*min-per-week (continuous score from the IPAQ scoring protocol) will be calculated following MET values per activity as proposed by Ainsworth et al. [37–39]. The IPAQ has been used previously in studies with cancer patients [40, 41], and has acceptable psychometric properties in terms of reliability and validity [42].

##### Stage of change

Stage of change is defined as motivational readiness towards a goal behaviour [27]. Participants will be asked: Which of the following statements fits you? 1) I’m not physicaly active and I’m not planning to become physicaly active within six months, 2) I’m not physicaly active and I’m planning to become physicaly active within six months, 3) I’m physicaly active but not regularly, 4) I’m physicaly active on a regular base but became this within the last six months, 5) I’m physicaly active on a regular base for more than six months [27].

##### Fatigue

Fatigue will be assessed with the Multidimensional Fatigue Inventory (MFI) [43]. The MFI consists of 20 items, categorized into five scales: general fatigue, physical fatigue, reduced activity, reduced motivation, and mental fatigue. The MFI is a valid and reliable instrument with internal consistencies ranging from 0.79 to 0.93 in cancer patients [44], which has been used in many studies with cancer patients as well as other populations [43].

##### Mood

Mood will be measured with the Profile Of Mood States (POMS) [45]. Mood will be measured with the shortened, 30-item version of the Profile of Mood States. Items are combined to form six separate subscales: tension-anxiety, depression-dejection, anger-hostility, vigour-activity, fatigue-inertia, and confusion-bewilderment. The subscale scores can be combined to form an overall measure of affect that is called total mood disturbance.

##### Health-related quality of life

We will measure HRQOL with the Medical Outcomes Study Short Form-36 (SF-36) [46]. This is the most widely used measure of general health status in clinical studies throughout the world. It generates scores in eight dimensions of HRQOL and two summary scores for physical and mental health. Additionally, for the purpose of CEA, we will administer the EQ5D-5 L. The EQ-5D health questionnaire is applicable to a wide range of health conditions and treatments. The instrument provides a simple descriptive profile and a single index value for health status. This health status is linked to utilities and is therefore used to calculate Qualify Adjusted Life Years (QALYs) for the cost-effectiveness analysis (CEA). The EQ-5D-5 L is primarily designed for self-completion by respondents and is ideally suited for use in postal surveys, in clinics and face-to-face interviews. It is cognitively simple, taking only a few minutes to complete [47].

##### Medical consumption questionnaire (iMCQ)

The iMCQ is a generic instrument for measuring medical costs. The iMCQ includes questions related to frequently occurring contacts with health care providers, which enables the estimation of the costs for the CEA from a societal perspective [48].

##### Productivity cost questionnaire (iPCQ)

The impact of disease on the ability of a person to perform work should be part of a cost-effectiveness analysis when a societal perspective is applied. The iPCQ is a generic instrument for measuring productivity (loss). The iPCQ includes questions related to the ability to perform and/or return to work after cancer diagnosis and treatment. In the current project, these question will only apply to patients who had a paid job at diagnosis [49].

#### Other outcomes

##### Socio-demographic and clinical data

The patients’ age, education, marital status, living situation, employment status, weight and height, medication and smoking status, and history of PA will be obtained via a questionnaire. Clinical information, including date of diagnosis, tumour characteristics, and treatment history (type of surgery, possible breast reconstruction, radiotherapy, chemotherapy, endocrine treatments) will be abstracted from the patients’ medical records. During the follow-up period, data on disease status (progression/recurrence), and any additional treatment will be obtained from the medical records.

##### Moderators and mediators of PA participation

Clinical and socio-demographic characteristics will be considered as moderators. As potentially mediating factors, data on behavioural variables related to PA will be collected through a questionnaire at baseline, 6 and 12 months. A series of questions will be asked regarding the attitudes towards PA, social support and self-efficacy. Patients’ preferences for type of exercise intervention will be assessed.

##### Non-participation analysis

We will ask non-participants if they would be willing to complete an online survey. If they consent, they will receive the survey containing the above questionnaires on socio-demographic and clinical characteristics, minutes of PA (IPAQ), stage of change, fatigue (MFI), mood (POMS), HRQOL (SF-36) and mediators of PA participation. We will also inquire about reasons for not participating. We will compare non-participants with trial participants, using baseline questionnaire data. This information can also be used for the cost-effectiveness analysis, to estimate the possible adherence and the real world use of the programs.

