#### Exclusion criteria

Main exclusion criteria are a lack of basic proficiency in Dutch, serious cognitive or psychiatric problems that would preclude following the intervention or completing the study questionnaires, and lack of internet access. Patients without a digital ID (DigID), which is a Dutch digital authentication code based on one’s social security number (mostly used for governmental services) will be excluded. DigID is one of the most frequently used authentication methods in the Netherlands. Also, patients participating in concurrent studies or rehabilitation programs containing psychosocial and/or exercise interventions will be excluded, as well as patients who are unable to perform unsupervised exercise at the recommended levels or who cannot safely perform such exercise according to the pre-exercise screening recommendations of the American College of Sports Medicine [23]. Patients who have (signs of) cardiovascular, metabolic, or renal disease, can only participate after approval by the treating physician. Lastly, because our aim is to increase PA-levels of cancer survivors, we will a-priori determine, by a short interview, who already meets the PA guideline of > 150 min MVPA/week of moderate to vigorous PA for more than 6 months. To take into account a ~ 30% overestimation of self-reported PA [24], we will be excluding patients who report > 200 min/week MVPA for longer than 6 months.

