### Recruitment and eligibility

In total, 246 patients will be recruited. We will include patients both retrospectively and prospectively. For the prospective part, the treating medical specialist or specialized nurse practitioners will inform the patient about the study during a follow-up appointment in the hospital. The clinician checks eligibility with the aid of a screening-list of inclusion and exclusion criteria. Interested patients will receive an information package. After two weeks, the researcher will contact the patient by phone to confirm whether or not the patient wants to participate. For the retrospective recruitment, eligible patients will be identified from medical records by the treating physician and will be sent study information by mail. If approved via a response card, the researcher will contact the patient by phone to confirm participation or non-participation.

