#### Non-participation analysis

Many trials on PA behaviour change interventions show recruitment rates of around 30% [25]. We expect that, in the current trial, a substantial percentage of eligible patients will also decline the invitation to participate. To gain more insight into the characteristics of this group, the non-participants will be invited to complete a one-time online questionnaire similar to the baseline questionnaire completed by study participants. In addition, we will ask them if they are willing to report their reason(s) for not participating.

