##### Non-participation analysis

The baseline measures of the participants of the study will be compared to those of non-participants using chi-squared statistic for categorical variables and analysis of variance for continuous variables.

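### Retrospective-route patients who decline on the response card have no described activity screen, so the non-participant comparison of activity and stage of change may partly reflect the screen

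*Protocol article*

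**What the plan says.** All references are to the protocol article.

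- **Exclusion criteria.** The activity screen is an interview: "we will a-priori determine, by a short interview, who already meets the PA guideline". Its cut-off allows for over-reporting: "we will be excluding patients who report > 200 min/week MVPA for longer than 6 months". The text does not say who holds the interview or at which recruitment step.
- **Recruitment and eligibility, prospective route.** Eligibility is checked at a follow-up visit, before the information package is given: "The clinician checks eligibility with the aid of a screening-list of inclusion and exclusion criteria".
- **Recruitment and eligibility, retrospective route.** Here "eligible patients will be identified from medical records by the treating physician and will be sent study information by mail". The first described contact with the researcher comes later: "If approved via a response card, the researcher will contact the patient by phone to confirm participation or non-participation".
- **Non-participation analysis, under Recruitment and eligibility.** The expectation is that "a substantial percentage of eligible patients will also decline the invitation to participate", and these people are invited to a one-time online questionnaire.
- **Non-participation analysis, under Other outcomes.** The survey covers IPAQ minutes, stage of change, fatigue, mood, SF-36 and mediators. The plan is: "We will compare non-participants with trial participants, using baseline questionnaire data".
- **Non-participation analysis, under Statistical analysis.** The method named for categorical items is as follows: "The baseline measures of the participants of the study will be compared to those of non-participants using chi-squared statistic". Continuous measures get an ANOVA. No restriction to decliners who would have passed the activity screen is stated.

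**The concern.** The participant group is cut off at the top on self-reported, sustained activity. If part of the non-participant group is not cut off in the same way, the two differ in activity even when the decision to take part has nothing to do with activity. Stage of change is affected too, because its last category is being regularly active for more than six months, which is the duration half of the screening rule.

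The comparison has stated uses. The Discussion lists it as a strength and expects it to show which patients are not reached, so that later programs can target them. The section on patients' evaluation uses it to improve the intervention. The survey section says it can also inform adherence and real-world use in the cost-effectiveness analysis. The Discussion fears that less motivated patients will be missed. Long-term active decliners in the survey push the result the other way and could mask that pattern. They also mix two kinds of people: those who could have joined and did not, and those who would have been excluded anyway. Only the first kind bears on uptake.

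**Working it through.** The article gives no sample size, power or expected difference for this comparison, so there is no stated figure to reproduce. The check is a reading of the two recruitment routes, followed by an illustration.

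**Step 1. Who has been screened on activity?**

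| Group | Described activity screen |
|---|---|
| Participants, both routes | Yes: the interview, with the 200 min/week and 6-month rule |
| Prospective decliners | Probably: exclusion criteria are checked before the information package, though the timing of the interview is not stated |
| Retrospective, decline by card | None described: eligibility comes from records, and the phone call follows only an agreeing card |

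A medical record is unlikely to hold six months of weekly MVPA minutes, which is presumably why the criterion calls for an interview.

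**Step 2. How large could the artefact be?** None of the following inputs is in the documents except the 200 min cut-off:
- weekly MVPA X in the source population is lognormal with median m = 90 to 150 min and log-SD s = 0.8 to 1.0;
- a share h = 0.5 to 1.0 of those above 200 min have been so for longer than 6 months;
- willingness to take part is unrelated to activity;
- a share u of responding decliners is unscreened.

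Under these inputs the screen removes 8% to 39% of candidates.

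Worked case with m = 120, s = 0.8, h = 1, u = 1 (Φ is the standard normal distribution function):
- z = ln(200/120)/0.8 = 0.6385, so the share removed is 1 − Φ(0.6385) = 0.26.
- Unscreened mean: 120 × exp(0.8²/2) = 165.3 min.
- Screened mean: 165.3 × Φ(0.6385 − 0.8)/Φ(0.6385) = 165.3 × 0.4359/0.7384 = 97.5 min.
- Spurious difference: 165.3 − 97.5 = 68 min/week (rounded).
- SDs: 156.5 unscreened and 47.7 screened. Pooled: √((156.5² + 47.7²)/2) = 115.7.
- Standardised mean difference (SMD): 67.7/115.7 = 0.58 to 0.59.

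The mean difference is proportional to u. Over the whole grid:

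| Share of responding decliners unscreened | Spurious difference, min/week | SMD |
|---|---|---|
| u = 1 | 18 to 151 | 0.17 to 0.70 |
| u = 0.5 | 9 to 76 | 0.08 to 0.35 |
| u = 0 | 0 | 0 |

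The u = 0.5 row keeps the denominator of the u = 1 row. Using the mixed group's own SD raises it somewhat. In the worked case the mixed variance is 0.5 × 156.5² + 0.5 × 47.7² + 0.25 × 67.7² ≈ 14,500, the pooled SD is √((14,500 + 47.7²)/2) ≈ 92, and the SMD is 33.9/92 = 0.37 instead of 0.29.

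**Step 3. Carry-over to outcomes that are not screened.** Approximate this as |correlation| × (difference in mean MVPA)/(SD of X). With an assumed correlation between fatigue and MVPA of −0.2 to −0.3, the artefact at u = 1 is 0.03 to 0.15 SD. It is 0 if the correlation is 0.

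**The case against.** **Eligible decliners.** The article describes non-participants as eligible patients, and eligibility includes the activity criterion. This does not settle the matter, because the retrospective paragraph uses the same word for patients found in records, before any interview.

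**All decliners unscreened.** A reader might infer that no decliner was ever screened on activity. The documents do not support that. The prospective route checks the exclusion criteria first, and the timing of the interview is open on both routes. The article also does not say how, or whether, card decliners are offered the survey. The point is therefore limited to card decliners who do respond.

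**Fatigue, mood and quality of life.** A reader might infer that these also differ by construction. They do not, since the screen uses only MVPA minutes and duration. Any carry-over needs a correlation that the documents do not give. Nor are age and education, which the Discussion also names, screening variables.

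**Data already in hand.** IPAQ minutes and stage of change are collected from non-participants, so the artefact can be examined at analysis. This stands in part. The IPAQ covers seven days and includes job, transport and household activity, and the stage item has no minutes threshold, so together they only approximate the interview. Filtering only the non-participants on them could create the opposite bias: participants who passed the interview but exceed 200 min on the IPAQ would stay, while similar decliners would go.

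**Left to the full protocol or analysis plan.** The timing of the interview may well be set out there. But the article itself fixes the groups, the instruments and the tests, and what the survey asks cannot be repaired at the analysis stage.

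**Conclusion.** The concern holds in a limited form. For patients who decline by card on the retrospective route, no activity interview is described, whereas every participant has passed one. To the extent that these decliners answer the survey, the planned comparison of self-reported activity and stage of change is partly a screening artefact.

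Its real size cannot be computed from the documents, because neither the split between routes nor the activity distribution is given. The SMDs above are illustrations under assumed distributions. They show that the artefact could reach what the article's own scale calls small to moderate with no true difference, and that it vanishes if all responding decliners were screened. The analysis is secondary and descriptive, and the randomised comparison is not affected. This is a cheap improvement, not a flaw in the trial's main inference.

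**What to change.** 1. Add the two screening questions to the non-participant survey: weekly MVPA minutes, and whether that level has lasted longer than 6 months.
2. In both Non-participation analysis sections (Other outcomes and Statistical analysis), compare participants with the non-participants who pass that same rule, and show the unrestricted comparison alongside.
3. If only the IPAQ and the stage-of-change item are available, apply one proxy rule to both groups as a sensitivity analysis: exclude anyone with more than 200 min/week MVPA who also reports being active for more than six months.
4. State at which step the activity interview takes place on each recruitment route.

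The cost is two survey items and a few lines of analysis text. The downside is a somewhat smaller comparison sample.

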##### Compliance

For both intervention groups, the number of questionnaires completed during IPAS or IPAS+TS, the duration of log-ins and navigation behaviour in the PA program (which pages were visited and for how long) will be collected from log data, which is a standard feature of the software of the hospital information system. In IPAS+TS, the number, duration and discussed topics of the telephone counselling sessions will be registered in the protocol by the physiotherapist. Furthermore, patients will be asked to complete a short questionnaire related to self-reported use of IPAS at 6 months. Scoring options will be either constructed as a 5-point Likert scale or as open ended responses. All patients, including those in the control group, will be asked if they have pursued any (other) activities relating to increasing their levels of PA (e.g., use of internet resources, self-help text books, physical therapy, etc.), during the period of the study. We will also ask the participants via which medium they most visited IPAS: computer, tablet or mobile phone.

##### Patients’ evaluation of the intervention program

At the 6-month assessment, the patients in the two intervention groups will be asked about their experience with the internet-based PA program. They will be asked to complete a short questionnaire about the perceived efficacy of and satisfaction with the intervention program, whether they would suggest any changes to the program, and if they would recommend it to other cancer survivors. Focus groups with a subset of participations may be held to provide some qualitative information as a supplement to the questionnaire data. Together with the non-participant analysis, we will use these data to further optimize the intervention.

